## Abstract

**Background:**

Sarcopenia is generally complicated with patients with chronic heart failure (CHF) and its presence negatively affects the course of heart failure, however effective nutritional intervention had not been elucidated yet. The primary objective of this study is to explore whether the addition of a branched-chain amino acid (BCAA) preparation for cardiac rehabilitation (CR) of patients with CHF further improves cardiopulmonary functions, skeletal muscle functions, and metabolism in comparison with conventional CR.

**Methods:**

This is a randomized, parallel-group comparative study. The elderly patients that were participated in CR and complicated with left ventricular systolic or diastolic dysfunction are randomized into two groups, CR + BCAA and CR. 20 weeks later, the second randomization is performed, which divide subjects into two groups with and without BCAA intervention without CR. Primary outcome measure is the rate of change of the anaerobic threshold workload from baseline to post-intervention. Secondary outcome include parameters of exercise capacity, cardiac function and psychological status.

**Discussion:**

In the current study the effect of a promising new intervention, BCAA, will be assessed to determine whether its addition to CR improve exercise capacity in patients with heart failure, who are generally complicated with sarcopenia.

**Trial registration:**

This clinical trial was registered with the University Hospital Medical Information Network—Clinical Trials Registry (UMIN–CTR; JPRN–UMIN R000022440).

## Background

Shortness of breath and labored breathing occur during daily activities in patients with chronic heart failure (CHF). These symptoms are caused by decreased systolic and diastolic cardiac function. Decreased exercise tolerance because of heart failure is also likely to be complicated with skeletal muscle weakness [1]. Indeed, the exercise tolerance of patients with CHF is known to be strongly related to skeletal muscle strength and muscle mass [2]. A decrease in skeletal muscle strength and muscle mass (sarcopenia) is an important factor that largely affects the subjective symptoms of patients with CHF. Furthermore, sarcopenia is generally complicated with several abnormalities such as metabolic disorders and decreased vascular function [3]. Sarcopenia is often induced by physical deconditioning because of rest during CHF treatment, and it can lead to a condition known as cachexia if concurrent metabolic disorders exist. Approximately 20% CHF patients are believed to suffer from sarcopenia, whereas 10% suffer from cachexia [4], and both are generally observed in elderly patients with cardiovascular disease [5]. Japan is experiencing an increasingly aging population; thus, CHF with coexisting sarcopenia and cachexia have become a big burden.

From the fact that 10%–50% of CHF patients who undergo a single pharmacotherapy intervention are repeatedly admitted for heart failure within a period of 3–6 months, it is evident that the presently available CHF treatments are quite insufficient. With a focus on sarcopenia and cachexia, cardiac rehabilitation is another comprehensive approach that improves cardiopulmonary functions, leading to the suppression heart failure events. Furthermore, in addition to an increase in exercise tolerance, cardiac rehabilitation has been shown to improve left ventricular function, endothelial function, and sympathetic activity, which may have favorable effects on the course of heart failure [6–10].

Branched-chain amino acid (BCAA) preparations have been available for purchase in the market since 1996 with the aim of correcting amino acid imbalance in the blood in patients with decompensated cirrhosis and improving hypoalbuminemia. BCAAs play an important role in the formation of skeletal muscles because they account for approximately 35% of the essential amino acids that form these skeletal muscles [11]. Indeed, BCAA preparations have been reported to promote postoperative wound healing and recovery from muscle fatigue after exercise and enhance muscle strength [12]. Its easily absorbable trait may also fit the treatment of heart failure, because patients with CHF often decreased digestive abilities because of cachexia. Furthermore, reports from animal experiments have revealed that BCAA had some positive effects on heart failure through the improvement on the function of the skeletal muscle mitochondria [13, 14]. Therefore, incorporation of BCAA in cardiac rehabilitation is expected to have additional effect on the improvement of cardiopulmonary and skeletal muscle functions. In this study, we hypothesized that the concurrent use of a BCAA preparation during cardiac rehabilitation has synergistic effects on the clinical course of CHF as well as improvement of skeletal muscle function, and metabolism. In addition, we would also like to investigate whether continued administration of the BCAA preparation after cardiac rehabilitation preserves cardiopulmonary function and skeletal muscles.

### Aim

The primary objective of this study is to explore whether the addition of a BCAA preparation for cardiac rehabilitation of patients with CHF further improves cardiopulmonary functions, skeletal muscle functions, and metabolism in comparison with conventional cardiac rehabilitation. In addition, we will also explore whether continued administration of a BCAA preparation after cardiac rehabilitation can preserve cardiopulmonary and skeletal muscles functions.

### Methods/Design

#### Patient enrollment

Patients with CHF was evaluated in the University of Tokyo Hospital and recruited if they fulfilled the following criteria: (1) Participation in a monitored cardiac rehabilitation program for CHF, (2) age ≥ 65 years, (3) experiencing left ventricular systolic dysfunction [ejection fraction (EF) <40% on echocardiography] or diastolic dysfunction (EF > 40% and E/e′ >15).

#### Exclusion criteria

A patient who meets any of the following criteria will not be included in the study: (1) presence of a congenital BCAA metabolism disorder, (2) presence of contraindications to cardiac rehabilitation, (3) pregnant or breast-feeding patient, (4) presence of other conditions, which make the patient unsuitable for the study according to the judgment of the principal investigator (PI) or coinvestigator (Co-I).

### Study methods

This is a randomized, active-controlled, parallel-group comparative study. Study outline is presented in Fig. 1. The study consists of three periods—pre-observation, intervention with concurrent cardiac rehabilitation, and BCAA single intervention. In pre-observation period (Day 1 to Week 4), the consent of patients undergoing cardiac rehabilitation at the hospital for CHF will be obtained, and their eligibility will be determined by blood tests and imaging tests (echocardiogram). In the period of intervention with concurrent cardiac rehabilitation (for 18–22 weeks), patients who are confirmed eligible for study enrollment will be randomized into either group A (CR + BCAA) or group B (CR). BCAA is orally supplemented with one pack of BCAAs granules (Aminovact Combination Granules ®, Nichi-Iko Pharmaceutical Co, Toyama, Japan) which includes 1144 mg of L-valine, 1904 mg of L-leucine and 952 mg of L-isoleucine, two times a day. Cardiopulmonary exercise test (CPX) will be performed on each subject in both groups before intervention with the BCAA preparation as well as at Week 14 and Week 20 of the intervention with cardiac rehabilitation. In the BCAA preparation single intervention period (20–24 weeks), re-randomization, i.e., randomization 2, will be performed after the cardiac rehabilitation program has ended. Subjects in group A will be assigned to Group A-1 or A-2, whereas those in Group B will be assigned to Group B-1 or B-2. As described in Fig. 1, subjects assigned to Group A-1 will continue the BCAA preparation. Similarly, subjects in Group B-1 will start taking the BCAA preparation. The BCAA preparation will be discontinued for subjects assigned to Group A-2, and subjects in Group B-2 will not undergo intervention with the BCAA preparation throughout the study period.

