### Enrollment and assignment

PI or Co-I will obtain the written consent of subjects. The enrollment of subjects who have given their consent and the data of all subjects will be entered into the electronic data capture (EDC) system (Viedoc, PCG Solutions, Uppsala, Sweden). For randomization 1, the subjects will be stratified into two groups (groups A and B as mentioned earlier) according to (1) age (>70 or ≤70 years) and (2) anaerobic threshold (AT) workload (≥30 watts or <30 watts) in the first CPX performed at the time of consent-taking. Randomization 2 will be performed after the intervention period with concurrent cardiac rehabilitation has ended. The stratification factors are (1) the age of the subject (>70 or ≤70 years) and (2) the rate of change in the AT workload in CPX after intervention with concurrent cardiac rehabilitation has ended (≥25% or <25% for group A and ≥15% or <15% for group B).

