### Statistical considerations

The sample size was calculated according to the estimation as follows. We hypothesized that following 6 months of cardiac rehabilitation, there will be an AT workload improvement of 25% (SD: 10%). With the addition of BCAA, we hypothesized that there will be an AT workload improvement of 25% (SD: 10%). Setting the two-sided significance level at5% and power at 90%, the required sample size was 43 cases. Assuming a 5% rate of subjects leaving the study, we chose 48 cases as the target number.

According to the study results, differences (%) in primary outcome between each outcome measurement between A and B groups will be evaluated using the t-test. With respect to differences in outcome measurement (%) in secondary endpoint between groups A and B, the t-test will be used to analyze statistical significance. Similarly, the difference between B-1 and B-2 sub-groups will be analyzed using the t-test. Also,, after confirming the assumption that there are no major differences among the treatment groups (no interaction), the two-way ANOVA will be used to test the treatment effect for addition of a BCAA, and maintenance effect for continuing administration of a BCAA by including group A/B and +1/+2 as factors. A box-plot will be used to visualize primary outcome and secondary outcomes between the 4 groups (A + 1, A + 2, B + 1, B + 2). Finally, defining an AT workload improvement of 15% as an event, a Kaplan–Meier curve will be plotted to compare the curves between groups A and B, and estimate the occurrence of an event rate of 50% of each group.

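### Training before baseline is neither limited, stratified nor adjusted for, and the first CPX has no stated link to the start of rehabilitation

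*Protocol article*

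**What the plan says.** All references are to the protocol article.

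- **Patient enrollment**, criterion 1: "Participation in a monitored cardiac rehabilitation program for CHF". No start date, maximum duration or number of sessions is given.
- **Exclusion criteria**: the only rehabilitation-related item is "presence of contraindications to cardiac rehabilitation".
- **Study methods**: during pre-observation (Day 1 to Week 4), "the consent of patients undergoing cardiac rehabilitation at the hospital for CHF will be obtained". Randomized subjects then have 18–22 weeks of concurrent rehabilitation, with tests at Weeks 14 and 20. The earlier test is tied to the start of BCAA, not of rehabilitation: "Cardiopulmonary exercise test (CPX) will be performed on each subject in both groups before intervention with the BCAA preparation".
- **Enrollment and assignment**: randomization 1 is stratified by age and by AT workload (cut at 30 watts) "in the first CPX performed at the time of consent-taking".
- **Outcome measures**: the primary endpoint is the percentage change in AT workload from baseline to the end of concurrent rehabilitation. Baseline is described only under the secondary outcomes, as falling in pre-observation or on a reference day that the text does not define.
- **Observations and examinations**: weekly rehabilitation visits are collected; a rehabilitation start date is not listed.
- **Statistical considerations**: the planning assumption is that "following 6 months of cardiac rehabilitation, there will be an AT workload improvement of 25% (SD: 10"%). Groups A and B are compared by an unadjusted t-test.

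**The concern.** The endpoint is a percentage gain from baseline, so it depends on how trained the patient already is when baseline is measured. Someone who has just begun and someone well into the program can both be enrolled. If gains level off with training, the second has less left to gain, from a baseline that is already raised. The AT workload stratum does not separate the two, because 30 watts can be a trained or an untrained value. The sample size, by contrast, borrows the gain expected from a 6-month course.

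The timing of the first test adds to this. If the consent test also serves as the endpoint baseline, which the text leaves open, up to 4 weeks of training without BCAA fall between baseline and randomization. This happens in both arms, so it creates no contrast between them, but its length can differ from patient to patient.

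At stake is the precision of the single primary comparison, and possibly the size of the difference it can show, in a trial of 48.

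**Working it through.** **1. The plan's own figure.** As printed, both arms gain 25% (SD 10%), so the difference is 0 and no sample size follows; that is a separate matter. To have a reference case, assume a 15% gain for rehabilitation alone, suggested by the 15% and 25% cut-offs for groups B and A at randomization 2 but not stated as the planning value. With a difference of 10, SD 10, two-sided 5% and 90% power:

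N = 2 × 2 × [(1.960 + 1.282) × 10 / 10]² = 42.03, or 22 per arm (44), against the stated 43.

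The target of 48 with 5% loss leaves 48 × 0.95 = 45.6, about 46 completers. The t-test power with 23 per arm is 0.91.

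**2. Timeline.** Pre-observation of up to 4 weeks plus 18–22 weeks is 22–26 weeks at most. That agrees with 6 months of rehabilitation only if Day 1 lies close to the start of rehabilitation, which no criterion requires.

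**3. What varies.** Everyone is planned for the same further 18–22 weeks. If gain accrued evenly, in percentage points of each patient's own baseline, prior weeks would make no difference and the added variance would be zero. An effect needs either a plateau or a raised denominator. The denominator alone does little: if gain were even in watts at 15% per 20 weeks (0.75 points per week), an assumed 12 prior weeks would turn 15% into 15 / 1.09 = 13.8%. A material effect therefore needs a plateau.

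**4. Illustration of a plateau (my assumptions).** Let f be the share of the full-course gain still available, uniform from f_min to 1. Its mean is m = (1 + f_min)/2 and its variance v = (1 − f_min)²/12.

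- Case A, both the rehabilitation gain and the BCAA effect shrink with f: difference 10m; SD = √(100 + ½(15² + 25²)v) = √(100 + 425v).
- Case B, only the rehabilitation gain shrinks: difference 10; SD = √(100 + 225v).

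For f_min = 0.5: m = 0.75 and v = 0.0208. Case A has difference 7.5 and SD 10.43; case B has difference 10 and SD 10.23.

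| f_min | A: difference | A: SD | A: power | B: SD | B: power |
|---|---|---|---|---|---|
| 1 | 10 | 10.00 | 0.91 | 10.00 | 0.91 |
| 0.75 | 8.75 | 10.11 | 0.82 | 10.06 | 0.91 |
| 0.5 | 7.5 | 10.43 | 0.66 | 10.23 | 0.90 |
| 0.25 | 6.25 | 10.95 | 0.47 | 10.51 | 0.88 |
| 0 | 5 | 11.64 | 0.30 | 10.90 | 0.86 |

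Power is for a two-sided t-test with 23 per arm. Chance imbalance in f is already contained in these SDs.

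**5. What adjustment can recover.** If a covariate removed all the added variance, case B would return to 0.91, before the loss of one degree of freedom. In case A at f_min = 0.5, power would rise only from 0.66 to 0.70 (difference 7.5, SD 10). Adjustment recovers precision; it does not restore a diluted difference.

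**The case against.** The strongest reply is that the plan's own timeline suits entry near the start of rehabilitation: 22–26 weeks in total matches 6 months, and a patient three months in would need some eight months before the program ended. Fig. 1 and Table 1 are not shown, and a condensed article may leave entry timing to the full protocol. This stands as a reason for caution about size. It does not supply the missing anchor, because the eligibility criteria as printed admit later entrants.

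A reader might infer that the endpoint mixes full and partial courses of rehabilitation. The article does not support that: the same 18–22 weeks follow randomization for all. A reader might also subtract prior weeks from a fixed course at an even rate and derive a definite power loss. That contradicts the schedule, which adds the weeks after enrolment; with even accrual nothing is lost.

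A reader might further take the consent test to be the primary baseline. The text ties it to stratification and leaves the endpoint baseline looser. Nor does anything show that late entrants could not reach the 15% or 25% thresholds.

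It is also fair to say that the planned SD of 10% might already include variation in prior training; the article does not say. Finally, randomization balances prior training in expectation, so no systematic bias between arms arises.

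**Conclusion.** The point holds in limited form. Prior training is neither limited nor stratified nor adjusted for, and the first exercise test, taken at consent and up to 4 weeks before randomization, is not linked to the start of rehabilitation. The assumed 6-month gain may therefore not apply to those who enter late.

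The consequence is extra variance, possible dilution and chance imbalance in 48 patients. Its size runs from negligible (even accrual, or case B with a modest spread) to material (case A with a wide spread). Which applies depends on the spread of entry times, on whether gains plateau, and on whether the BCAA effect shrinks with them. The document gives none of these, so no single power figure should be attached. The illustration also rests on an assumed 10-point difference.

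This is a cheap improvement in precision, not a flaw that invalidates the comparison.

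**What to change.** 1. Take the already planned pre-intervention CPX at the end of pre-observation, immediately before randomization 1. Use that one test both for the AT workload stratum and as the baseline of the primary endpoint, and say so under Outcome measures.
2. Record the date on which each patient's current rehabilitation program began.
3. Replace the unadjusted t-test of A versus B with a prespecified linear model containing treatment group and weeks of rehabilitation completed before the baseline test.

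The cost is one recorded date, one degree of freedom and tighter scheduling of a test that is already planned. A limit on prior training at entry is optional: it would make the population more uniform, at the price of slower recruitment and a narrower question, and the point does not require it.

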**Fig. 1 Fig1:**
[figure not shown]
Schematic of study design

This clinical study is in accordance with International Conference on Harmonization of technical requirements for registration of pharmaceuticals for human use (ICH-GCP). Furthermore, the clinical study is conducted with strict observance of ethical guidelines and the latest Declaration of Helsinki. This clinical trial was registered with the University Hospital Medical Information Network—Clinical Trials Registry (UMIN–CTR; JPRN–UMIN R000022440). Also, the protocol was approved by the institutional review board of Tokyo University Hospital.

### Enrollment and assignment

PI or Co-I will obtain the written consent of subjects. The enrollment of subjects who have given their consent and the data of all subjects will be entered into the electronic data capture (EDC) system (Viedoc, PCG Solutions, Uppsala, Sweden). For randomization 1, the subjects will be stratified into two groups (groups A and B as mentioned earlier) according to (1) age (>70 or ≤70 years) and (2) anaerobic threshold (AT) workload (≥30 watts or <30 watts) in the first CPX performed at the time of consent-taking. Randomization 2 will be performed after the intervention period with concurrent cardiac rehabilitation has ended. The stratification factors are (1) the age of the subject (>70 or ≤70 years) and (2) the rate of change in the AT workload in CPX after intervention with concurrent cardiac rehabilitation has ended (≥25% or <25% for group A and ≥15% or <15% for group B).

### Outcome measures

Primary outcome measure is the rate of change of the AT workload from baseline to post-intervention with concurrent cardiac rehabilitation. Secondary outcome measures include the following: (1) The rate of change from baseline which is performed in the pre-observation period or reference day [Peak VO_2,_ left ventricular EF in the echocardiogram, total points of the Hospital Anxiety and Depression Scale (HADS), muscle strength (grip strength and lower-limb extension power), absolute values of interleukin-6 (IL-6), and tumor necrosis factor (TNF)-α], Time taken for 50% subjects to achieve a 15% improvement in AT workload, which is defined as an event. (2) The rate of change from post-intervention period with cardiac rehabilitation (20 weeks later) to post-single intervention with the BCAA preparation (32 weeks later) [Peak VO_2_, AT workload, total points of HADS, muscle strength (grip strength and lower-limb extension power))], (3) The frequency of serious adverse events (SAEs) throughout the study period.

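### Percent change is a poor metric for HADS total points, and the metric for IL-6 and TNF-α is not fixed

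*Protocol article*

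**What the plan says.** In the Protocol article, Outcome measures, the first group of secondary outcomes is headed "The rate of change from baseline which is performed in the pre-observation period or reference day". One bracket under that heading holds peak VO2, LVEF, "total points of the Hospital Anxiety and Depression Scale (HADS), muscle strength (grip strength and lower-limb extension power), absolute values of interleukin-6 (IL-6"), and TNF-α.

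The second group is the rate of change from the end of rehabilitation (20 weeks) to the end of the BCAA-only period (32 weeks). It again includes HADS: "Peak VO_2_, AT workload, total points of HADS, muscle strength (grip strength and lower-limb extension power").

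Statistical considerations gives the scale and the test: "With respect to differences in outcome measurement (%) in secondary endpoint between groups A and B, the t-test will be used". The B-1 versus B-2 comparison is to be handled in the same way.

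Enrollment and assignment shows what rate of change means in this article. For AT workload it is cut at percentages: "≥25% or <25% for group A and ≥15% or <15% for group B".

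**The concern.** The words percent change from baseline do not appear for HADS. They follow from three places read together: the rate-of-change heading, the percent sign in the analysis sentence, and the percent cut-offs used for the same term in the randomisation section.

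A percent change divides by the baseline value. That is reasonable for a quantity well away from zero, such as workload or strength. It suits a points score poorly if the score can be zero or very small: the result is then undefined, or a shift of one or two points becomes a very large percentage. The entry and exclusion criteria do not require anxiety or depressive symptoms, so low HADS scores are plausible. In the second period the denominator is the week-20 score, and the same problem arises in smaller groups (48/4 = 12 per subgroup if the split is even).

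The cytokine problem is one of wording. A reference to absolute values sits in a list of rates of change, and the analysis sentence then gives a percent scale for secondary endpoints. Level, absolute change and percent change all remain open, and it is unclear whether the qualifier covers TNF-α as well as IL-6.

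At stake are the efficiency and clarity of the HADS comparison, and the freedom to choose a cytokine metric after the data are seen.

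**Working it through.** The article gives no figure for these endpoints, so there is none to reproduce. Its sample-size calculation concerns the primary endpoint only.

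**1. How percent change behaves.** Formula: 100 × (follow-up − baseline) / baseline.

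- HADS 1 to 3: 100 × 2/1 = +200%.
- HADS 20 to 15: 100 × (−5)/20 = −25%.
- HADS from 0: division by zero.
- LVEF 25 to 30: 100 × 5/25 = +20%.
- LVEF 60 to 65: 100 × 5/60 = +8.3%.

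A 2-point worsening in one low scorer therefore carries eight times the weight (200/25) of a 5-point improvement in a high scorer. For LVEF the weight varies with baseline but stays moderate.

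**2. How often a zero baseline would occur.** Assumptions, none from the article: HADS total runs from 0 to 42, and baseline is negative binomial with mean m and SD s. Then k = m²/(s² − m), p = k/(k + m), P(0) = p^k, and the chance of at least one zero among the 48 target patients is 1 − (1 − P(0))^48.

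| m / s | k | p | P(0) | expected zeros in 48 | at least one zero | score 3 or less |
|---|---|---|---|---|---|---|
| 7 / 5 | 49/18 = 2.72 | 0.280 | 0.0313 | 1.5 | 78% | 27% |
| 9 / 6 | 81/27 = 3.00 | 0.250 | 0.0156 | 0.75 | 53% | 17% |
| 12 / 6.5 | 144/30.25 = 4.76 | 0.284 | 0.0025 | 0.12 | 11% | 6% |

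**3. What the percent scale costs in power.** Further assumptions: true effect −2 points, SD of change 3 points, 22 per arm, two-sided 5% level, patients with baseline 0 left out of the percent analysis.

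A rough check for the points scale: (2/3) × √(22/2) = 2.21, so power is about Φ(2.21 − 1.96) = Φ(0.25) = 0.60. The t distribution, rounding to whole points and the floor at zero bring this down somewhat.

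- Simulated power, t-test on percent change: about 41–44%.
- Simulated power, points (change score or ANCOVA): about 54–56%.

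A repeat of the simulation moved the ends of these ranges by no more than about 2 percentage points. A separate run with 21 per arm and baselines 8/5, 10/6 and 12/7 gave 40–42% on percent change, against 53–55% on change in points and 52–54% with ANCOVA. With less noise (SD 2.5, 22 per arm) the figures were 53–57% and 68–72%. The level of power depends on the assumptions. The loss was in the same direction in every scenario, at roughly 10 to 15 percentage points.

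In these simulations ANCOVA gains nothing over the simple change in points, because follow-up was generated to track baseline one for one. The gain comes from leaving the percent scale. ANCOVA also adjusts for chance baseline imbalance.

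**4. Cytokines.** No arithmetic applies. Outcome measures states rate of change in the heading and absolute values in the item. Statistical considerations states a percentage. No single metric satisfies all three.

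**The case against.** The strongest case against has four parts.

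- **The HADS argument rests on facts outside the article.** The zero floor, the baseline distribution and the noise are all assumed, and the wide range of 11–78% shows it. At most 1.5 zero baselines would be expected in the whole trial. This stands as a limit on the size of the problem. It does not rescue the metric, because low non-zero baselines also distort it and power fell in every scenario tried. A reader might infer that patients scoring 0 are to be dropped. The article states no such rule. Exclusion is one possible consequence of an undefined value, and its handling may properly sit in an analysis plan that is not shown.
- **The cytokine wording is probably a deliberate exception.** Only these two markers carry the qualifier, and the percent sign cannot literally cover every secondary outcome, since adverse-event frequency is among them. That is the natural reading. Even so, the analysis section does not carry the exception through, and it stays unclear whether level or absolute change is meant. A reader might go further and infer that a few high cytokine values would drive the t-test. The documents give no cytokine distribution, so that cannot be claimed.
- **LVEF does not share the HADS problem.** This stands. Eligibility is "experiencing left ventricular systolic dysfunction [ejection fraction (EF) <40% on echocardiography] or diastolic dysfunction (EF > 40% and E/e′ >15"), so EF is not near zero and percent change is always defined. Both arms come from the same randomised population, so the comparison is not biased by the EF mix. Calling the LVEF endpoint undefined or outlier-driven would be wrong. What remains is dependence on baseline and possible confusion of relative percent with percentage points.
- **ANCOVA and log scales are analysis-plan detail.** Their absence from a condensed article is no fault. The point here is that the article does state a metric and a test, and the metric is ill-suited to HADS and inconsistent for the cytokines.

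**Conclusion.** The point holds for HADS and for the cytokine wording, and only in a mild form for LVEF.

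- **HADS:** the stated method is a t-test on percent change, in both periods. If the score can be 0 or near 0, that method can be undefined and gives low baselines undue weight. Under the assumed inputs it gives up roughly 12 percentage points of power for a 2-point effect (about 54–56% down to 41–44%). The exact size depends on distributions that the article does not give.
- **IL-6 and TNF-α:** the metric is not fixed. An intended exception to the percent scale is likely, but it is not stated consistently.
- **LVEF:** always defined. The issue is one of scale and clarity.

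The primary endpoint and the sample size do not depend on any of this. It is worth correcting, but it does not threaten the trial's main comparison.

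**What to change.** 1. Analyse HADS total in points, by ANCOVA on the follow-up value with treatment group and the baseline score as terms. For weeks 20 to 32, use the week-20 score as the covariate.
2. Preferably treat LVEF the same way and label the result in percentage points.
3. State one metric for IL-6 and TNF-α and say that it covers both. One suitable choice is the log follow-up value adjusted for log baseline, reported as a ratio between groups.
4. Make Outcome measures and Statistical considerations agree, so that each secondary endpoint has one stated scale and the percent sign applies only where percent change is meant.

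The cost is wording in the endpoint list and the analysis text. No extra data, visits or patients are needed. The one loss is a common percent scale across the secondary endpoints; percent change can still be shown descriptively for strength and peak VO2. The change should be made and dated before outcome data are examined by group.
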